##### Construct/Discriminant Validity

Construct validity is the degree to which an instrument measures an intended construct. Multiple regression will be used to examine the discriminant validity of the proposed subscales and possible support for the multidimensional conceptualization of satisfaction. Scores on the general satisfaction subscale will be used as the outcome variables and other subscale scores will be used as predictor variables.

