#### AIMS Pilot Test

We will conduct mock tests of the AIMS Internet instrument and analyze the questions for logistical problems such as skip patterns, range errors, and response issues. Once all logistical issues are resolved, we will pilot the AIMS Internet survey with a sample of 50 American Indian/Alaskan Native women. The pilot testing procedure described below will allow us to administer the AIMS to a sample of women to determine if the questions are presented in a clear and understandable manner, assess the face validity of the questions, and evaluate the survey administration procedure. The pilot test will help guide the final refinement of the AIMS.

After completing the AIMS web survey, additional questions will be tagged on the end of the assessment that inquire about: 1) whether participants felt the survey questions clearly assessed the important aspects of mammography services, mammography satisfaction and dissatisfaction, and barriers to mammography utilization, 2) whether participants felt comfortable responding to all of the questions, 3) perceptions regarding the clarity and completeness of the information included in the AIMS survey, 4) the personal relevancy of the survey topics, and 5) the readability/presentation of the AIMS survey. Survey items will be revised based on feedback and re-piloted with additional participants until an acceptable AIMS survey has been developed.

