### Study 3: Assessment of Variation in American Indian Mammography Satisfaction

#### Full AIMS Implementation Procedure

##### AIMS Recruitment

As with the focus group and AIMS pilot testing portions of this study, AIMS survey participants will be recruited at the Haskell Health Center through referral from clinic personnel and through posters in the waiting area. We will also recruit at 4-5 AI/AN community events held each year (one event in each of the four Kansas-based reservation cities (e.g., Horton, White Cloud, Mayetta, and Reserve, KS). These community events will include health fairs and Pow Wows. This multi-method plan of recruitment will allow us better access to participants who do not use IHS facilities for mammograms. In advance of events, we will post flyers and posters at various community locations in the four primary Kansas Indian Reservation sites and at the Haskell Health Center. We will also post informational flyers at other local AI/AN venues including the Heart of America Indian Center and the offices of the American Indian Council. We will make two Internet-ready laptop computers available at each community event so that interested participants readily may complete the AIMS survey. Postcards with the Healthy Living American Indian Women website address will be provided to those women who express interest but who prefer to complete the assessment in the comforts of another environment (e.g., their home or local library). An additional paper and pencil version of the AIMS survey will be available on site at community recruitment events for those individuals preferring a non-electronic information submission approach.

The Principle Investigator and Project Manager will maintain close contact with key community member stakeholders involved in the proposed recruitment venues and will conduct ongoing assessments of the feasibility of the procedure used to identify women for the AIMS survey. Appropriate adjustments in the recruitment protocol will be made to meet survey accrual needs.

Eight to 10 subjects per AIMS survey item will be used during this study (for example, if 25 items are included in the instrument, 200-250 patients will be used). We will mail postcard reminders and telephone persons who were recruited and expressed an interest in participating in the AIMS on their own time but who fail to engage with the survey to maximize recruitment efficiency and survey completion.

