##### Mammography Satisfaction Variation

We will use descriptive statistics to explore the extent to which the mammography experiences and mammography satisfaction of American Indian/Alaskan Native women vary. Frequencies and percentages will be used to summarize categorical demographic information of the participants surveyed. The primary outcome will be the global satisfaction score on the AIMS with secondary outcomes being the derived AIMS subscales. AIMS subscales will be derived from barriers cited by focus group participants and confirmed through factor analytic procedures conducted during the AIMS pilot test. Projected subscales will include service accessibility, results reporting procedures, staff interpersonal skills, perceived technical competence of staff, and global satisfaction. To model the global AIMS scores on individuals adjusting for individual factors (age, race/ethnicity, etc.), linear regression models will be developed. Similar models will be developed for AIMS subscale scores.

Using global patient satisfaction as the primary outcome variable, we also then conduct comparison of AIMS survey characteristics between women who sought services within and outside of the Indian Health Service system. This will be done by averaging the global AIMS scores for participants with an Indian Health Service-sponsored mammogram and those with a non-Indian Health Service-sponsored mammogram. Similar averaging will be done for each AIMS subscale to obtain global AIMS subscale scores.

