##### Sample Size Justification

Specific Aim 3 of this study is to assess the difference in satisfaction of mammogram experiences between American Indian women who had mammogram in facilities affiliated to the Indian Health Service (IHS) and American Indian women who had mammogram in facilities not affiliated to the HIS. The sample size is justified based on the global satisfaction score of the questionnaire developed in Specific Aim 2 for satisfaction regarding the mammogram experience. Assuming the total score follows normal distributions and a frequency distribution of 10% (women with mammograms from IHS facilities) and 90% (women with mammograms from non-IHS facilities) in these two groups, a total sample size of 300 American Indian women, expected to be 30 from IHS-affiliated and 270 from non-IHS-affiliated institutions, will provide 80% power at 0.05 significance level to detect an effect size of 0.54 in the total score of satisfaction according to a two-sided two-sample t-test.

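### The regression planned for discriminant validity tests what predicts general satisfaction, not whether the subscales are distinct from one another

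*Protocol article*

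**What the plan says.** The section Construct/Discriminant Validity names one method: "Multiple regression will be used to examine the discriminant validity of the proposed subscales and possible support for the multidimensional conceptualization of satisfaction". It then specifies the model: "Scores on the general satisfaction subscale will be used as the outcome variables and other subscale scores will be used as predictor variables". It gives no rule for reading the output (overall fit, each coefficient, or something else), and it does not mention correlations among the predictor subscales.

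The section Mammography Satisfaction Variation makes the global score the primary outcome and the subscales secondary outcomes, with separate regression models and separate averages for women with IHS and non-IHS mammograms. It lists the expected scales: "Projected subscales will include service accessibility, results reporting procedures, staff interpersonal skills, perceived technical competence of staff, and global satisfaction". That leaves four predictors once the satisfaction scale is taken as the outcome.

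Factor analysis appears in two other places. The Reliability section uses an exploratory version under the heading of reliability and for naming factors. Mammography Satisfaction Variation says that factor analysis during the pilot will confirm the subscales; the AIMS Pilot Test section states "we will pilot the AIMS Internet survey with a sample of 50 American Indian/Alaskan Native women". Neither place connects it to the discriminant-validity conclusion.

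Two sample sizes are relevant. Sample Size Justification gives "a total sample size of 300 American Indian women, expected to be 30 from IHS-affiliated and 270 from non-IHS-affiliated institutions". AIMS Recruitment gives "Eight to 10 subjects per AIMS survey item will be used during this study", which its own 25-item example turns into 200 to 250 women.

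**The concern.** Discriminant validity asks whether scales that are meant to measure different things really do so. The evidence lies in the correlations among those scales, allowing for measurement error. The planned regression answers another question: which subscales carry information about general satisfaction.

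The two questions can come apart in both directions. A well-separated subscale that has nothing to do with general satisfaction, or with the other subscales, has an expected coefficient of zero and would look unsupported. Several noisy readings of one construct can each earn a significant coefficient, because each adds a further reading of that construct and so reduces noise.

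At stake is Aim 2, which is to validate the survey's psychometric properties, and the interpretation of the secondary subscale outcomes. If subscales that are not distinct were accepted as distinct, a single finding could be reported as several.

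**Working it through.** **1. The plan's own figure.** Construct/Discriminant Validity states no number. The only power statement is in Sample Size Justification: "80% power at 0.05 significance level to detect an effect size of 0.54", for a "two-sided two-sample t-test" with 30 and 270 women.
- Standard error of the standardised difference: sqrt(1/30 + 1/270) = 0.1925.
- 0.54 / 0.1925 = 2.806; 2.806 − 1.960 = 0.846; normal probability 80.1%. The exact noncentral t (298 df) gives 79.9%.

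The figure is reproduced. It is used here only to fix N = 300.

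**2. Inputs not in the document.** Correlations and reliabilities are not given and are assumed, over a range. Let r be the common correlation among k = 4 subscales and c their common correlation with general satisfaction.
- Coefficient: b = c / (1 + 3r)
- Fit: R² = 4cb
- Variance inflation: VIF = 1 / (1 − 3r²/(1 + 2r))
- Standard error: SE = sqrt((1 − R²) × VIF / 295), with 295 = 300 − 4 − 1
- Expected t = b / SE

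**3. Same inter-subscale correlation, opposite results.** Take r = 0.85 in both columns, so the relation among the subscales is identical (VIF = 5.07).

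| | c = 0.85 (general satisfaction is an equally reliable measure of the same factor) | c = 0.70 |
|---|---|---|
| b | 0.85/3.55 = 0.239 | 0.70/3.55 = 0.197 |
| R² | 0.814 | 0.552 |
| SE | 0.0565 | 0.0877 |
| Expected t | 4.24 | 2.25 (p = 0.025) |
| All four coefficients significant (simulated, two-sided 0.05) | about 95% | about 3% |

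An expected t of 2.25 is only just above the critical value, so it does not mean that all four tests succeed together. In the right-hand setting, two or fewer coefficients are significant in about 52% of samples.

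**4. One true factor, range of r (c = r).** Simulated proportion with all four coefficients significant:
- N = 300: 89%, 93%, 96% and 97% for r = 0.70, 0.80, 0.90 and 0.95
- N = 250: 82% to 91%
- N = 200: 59% to 75%
- N = 50: about 0%

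The overall F-test is significant in 100% of samples at every N. With five predictors and N = 300, all five are significant in 51% to 67%. Repeat runs differ by a percentage point or two.

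**5. One near-duplicate pair among otherwise distinct subscales** (other correlations 0.3; each 0.5 with general satisfaction; N = 300). Both members of the pair are significant in 94% of samples at pair correlation 0.6, 40% at 0.8, 1.7% at 0.9 and 0.15% at 0.95. The overall F-test is again significant in 100%.

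**6. Contrast with a direct check.** In step 4 each subscale's reliability equals r, so the corrected correlation is r / sqrt(r × r) = 1.00 in every setting. It would flag the subscales as not distinct where the regression usually passes them.

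**The case against.** **Near-duplicates often fail.** A reader might infer that near-duplicate subscales would always pass. The calculations do not support that. Collinearity inflates the standard errors, and in step 5 and the right-hand column of step 3 redundant subscales rarely all reach significance. This objection stands and limits the claim: redundant subscales can pass, depending on the correlations and on a criterion that the article does not state. It does not rescue the method, because the outcome then turns on the relation to general satisfaction and not on distinctness.

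**Factor analysis is planned.** A reader might also infer that nothing in the plan could reveal merged dimensions. That is too strong. The exploratory analysis in the Reliability section, listed among the Study 3 analyses, and the factor analysis in the pilot could both show subscales collapsing together. They are a partial safeguard. The first is labelled as reliability. The second starts from 50 women, which is 50/25 = 2 per item in the article's own 25-item example, against its rule of 8 to 10. Re-piloting may add some participants. Neither is tied to the validity conclusion.

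**The wording is cautious and the article is condensed.** The text claims only possible support, and no decision to keep or merge subscales hangs on the regression. Correlation tables and model comparisons are often left to a full analysis plan. Their absence alone is not the finding. The finding is that the article names a specific method for this purpose, and the method answers a different question.

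**Redundancy is not shown.** It would be tempting to say that five reported outcomes are really one. The documents give no correlations, and the list of five includes the satisfaction scale itself.

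**Conclusion.** The concern holds in this form: the planned regression measures prediction of general satisfaction and cannot by itself establish that the subscales are distinct or that satisfaction is multidimensional. This follows from the model's structure and needs no assumed number.

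The size does need assumptions. With four subscales, N = 300 and two-sided 0.05 tests, subscales that all measure one factor have every coefficient significant in about 89% to 97% of samples when general satisfaction measures that factor equally reliably (r from 0.70 to 0.95). With r = 0.85 and a correlation of 0.70 with general satisfaction, the figure is about 3%. The spread at a fixed inter-subscale correlation of 0.85 (95% against 3%) is the point, because the result moves while the relation among the subscales does not.

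The consequence is confined to Aim 2 and the secondary subscale outcomes. The primary IHS versus non-IHS comparison of the global score, and its sample size, are untouched. The change is worth making, but nothing here threatens the study's main comparison.

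**What to change.** In Construct/Discriminant Validity, base the conclusion on two analyses in the main AIMS sample:

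1. The matrix of inter-subscale correlations, corrected for unreliability using each subscale's estimated reliability.
2. A comparison of a one-factor model with the proposed multi-factor model.

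State in advance the limit above which two subscales are treated as not distinct, and what follows for their reporting as secondary outcomes. A latent correlation of 0.85 is one example; the documents do not supply a value, so the investigators should choose and justify theirs.

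Keep the regression, described as an account of what drives general satisfaction. Add a sentence linking the factor analysis already mentioned under Reliability and Mammography Satisfaction Variation to the discriminant-validity conclusion, and say in which sample it is run.

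The cost is revised wording and a little more analysis work. No new data, participants or survey items are needed.

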##### Reliability

The test-retest reliability, or reproduciblity, of a survey instrument refers to its ability to consistently measure all domains of diseases-specific functional status over time in a stable cohort of patients [98-100]. The more reliable, or reproducible, a measure is, the smaller the required sample size for meaningful applications of the questionnaire. Exploratory factor analysis will be used to measure reliability (using Cronbach's coefficient alpha [101]). The existing scales from the Cockburn and PAMS instruments as well as constructs derived from the focus groups will be used as the theoretical basis for naming factors revealed by this factor analysis.

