##### Internal Consistency

Data will be analyzed for internal consistency within domains to demonstrate the appropriate clustering of items. Each domain will be individually assessed using Cronbach's alpha, the standard statistical technique for assessing the coherency of each item within each domain.

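### The Reliability section defines test-retest reproducibility but names exploratory factor analysis and Cronbach's alpha, which use one occasion and cannot estimate it

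*Protocol article*

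**What the plan says.** Under Data Analysis in Study 3, the protocol article treats internal consistency and reliability in separate sections.

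- **Internal Consistency:** "Each domain will be individually assessed using Cronbach's alpha". The stated purpose is to show that items cluster properly within their domains.
- **Reliability, definition:** "The test-retest reliability, or reproduciblity, of a survey instrument refers to its ability to consistently measure all domains", and the definition continues "over time in a stable cohort of patients". No other kind of reliability is defined there.
- **Reliability, method:** "Exploratory factor analysis will be used to measure reliability", with Cronbach's coefficient alpha given in parentheses. The factors are to be named from the existing Cockburn and PAMS scales and from the focus-group constructs.

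On repeated use of the survey, the AIMS Pilot Test section says "Survey items will be revised based on feedback and re-piloted with additional participants until an acceptable AIMS survey has been developed". The AIMS Recruitment section sends reminders to interested women who have not yet engaged with the survey. Neither describes the same woman completing it twice.

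**The concern.** The property defined and the method assigned to it do not match. Test-retest reliability concerns whether the same stable respondents give the same scores on two occasions. Exploratory factor analysis and alpha are both computed from the item covariances of one occasion, so they carry no information about change between occasions.

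Aim 2 is to validate the instrument's psychometric properties. If alpha from the Reliability section were reported under the definition given there, readers of the validation could take a high alpha as evidence that the score is stable over time. An instrument with a high alpha can have poor stability.

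**Working it through.** **1. Is there a stated figure to reproduce?** The article gives none for reliability. Its only power figure is in Sample Size Justification: 30 versus 270 women, effect size 0.54, two-sided 0.05, power 80%. This reproduces at 80.1% (normal approximation) and 79.9% (noncentral t). No reliability coefficient enters it, so that calculation is unaffected.

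**2. Definition against method.**

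| Element | Reliability section | Occasions needed |
|---|---|---|
| Property defined | Test-retest reproducibility in a stable cohort | Two or more, same women |
| Method: exploratory factor analysis | Dimensionality of the items | One |
| Method: Cronbach's alpha | Covariation of items within a scale | One |

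**3. Is a second occasion described anywhere in the article?**
- Pilot: re-piloting uses additional participants, and follows revision of the items. It is not a retest.
- Full survey: reminders go to women who have not engaged. They ask for a first completion.
- Unique ID (Survey Form Development): it lets a woman save an unfinished survey and return to finish it. That is one completion in parts.
- No retest interval, retest subsample, ICC or test-retest correlation appears.

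**4. How little alpha says about stability.** The parameters are assumed for illustration and do not come from the article: k = 5 items, common-factor variance 1, item error variance 1, and a share p of the factor variance that is stable between occasions.

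- Variance of the sum score on one occasion = k² × 1 + k × 1 = 25 + 5 = 30.
- Alpha = k/(k − 1) × (1 − sum of item variances / 30) = 5/4 × (1 − 10/30) = 0.833. It does not involve p.
- Covariance of the two sum scores = 25p, so test-retest ICC = 25p/30 = 0.833p.

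| Stable share p | Alpha, one occasion (simulated) | Test-retest ICC (simulated) | 25p/30 |
|---|---|---|---|
| 1.00 | 0.833 | 0.833 | 0.833 |
| 0.75 | 0.834 | 0.626 | 0.625 |
| 0.50 | 0.833 | 0.418 | 0.417 |
| 0.25 | 0.836 | 0.209 | 0.208 |
| 0.00 | 0.834 | 0.001 | 0.000 |

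The simulation (200,000 respondents per row) agrees with the algebra. The same alpha fits any test-retest ICC from 0 to 0.83.

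**5. What a retest would give.** Assume an observed ICC of 0.80 with two measurements per woman (one-way model). F₀ = (1 + 0.80)/(1 − 0.80) = 9. The limits are (F − 1)/(F + 1), with F_L = F₀ / F₀.₉₇₅(n − 1, n) and F_U = F₀ × F₀.₉₇₅(n, n − 1).

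- n = 50: F_L = 9/1.756 = 5.13, giving 4.13/6.13 = 0.67. F_U = 9 × 1.759 = 15.83, giving 14.83/16.83 = 0.88.
- n = 30: F_L = 9/2.083 = 4.32, giving 3.32/5.32 = 0.62. F_U = 9 × 2.092 = 18.83, giving 17.83/19.83 = 0.90.

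**The case against.** The best defence is that the sentence naming the method says reliability in general, and internal consistency is a recognised form of reliability. The definition before it speaks of disease-specific functional status and of patients. That does not describe a mammography satisfaction survey, so it may be generic background and not a commitment. This has some force, but it does not rescue the section. Test-retest is the only form of reliability defined there, internal consistency has its own section, and on the charitable reading the definition is still wrong for the analysis and must go.

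Four stronger readings are tempting and are not supported:

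- **That the same alpha is reported twice.** Internal Consistency applies alpha to domains, and Reliability applies it alongside factors still to be derived. If the groupings differ, so do the coefficients. The overlap is in method only.
- **That the plan commits to claiming reproducibility.** No sentence says that reproducibility will be reported, and Aim 2 does not name test-retest. The claim is a risk created by the wording.
- **That a single administration is a stated design feature.** The article merely describes no repeat, and a fuller protocol could contain one. The mismatch does not depend on this: even with two administrations, factor analysis and alpha would not estimate reproducibility.
- **That the study's main result is undermined.** The primary outcome is the global AIMS score, and the sample size rests on comparing it between IHS and non-IHS women. Neither uses a test-retest coefficient.

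**Conclusion.** The point holds as a mismatch between definition and method within the Reliability section. The named analysis cannot estimate the property defined, and any reproducibility conclusion drawn from it under Aim 2 would be unsupported. This is a stated method that is wrong for its purpose, not detail left to a fuller document.

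In size, the planned analysis gives no information on test-retest reliability. The 0-to-0.83 range is an illustration under assumed parameters and does not predict how AIMS will behave. No stated number in the article is wrong. The point should be fixed because it governs what the validation can conclude, but it is not critical to the trial.

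**What to change.** **Minimum change, wording only.** In the Reliability section, report alpha for the derived factors as internal consistency. Present the exploratory factor analysis as evidence on dimensionality and construct validity. Remove the test-retest definition and make no reproducibility claim. This costs nothing in data collection.

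**Only if reproducibility is to be claimed.** Add a repeat administration in a stable subsample at a stated interval, and report the ICC with its 95% CI for the global score and each subscale. The article gives neither a target ICC nor a retest sample size, so both must be chosen and justified; the intervals worked out above for 50 and 30 women show the precision to expect if the ICC is 0.80.

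The cost of this option cannot be settled from the article. The portal would have to accept a second completion, and the article describes the ID only for resuming an unfinished survey. The plan should also say whether women who answer on paper are included in the retest.
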